## Abstract

**Background:**

Plant- and insect-based foods are promising alternative protein sources. Previous studies have shown that introducing plant-based foods to the diet can reduce meat intake, but no such intervention has explored the effects of insect-based foods.

**Methods:**

This study aims to integrate alternative proteins to main meals of 80 Danish families through a 6-week two-arm randomized intervention trial to investigate acceptance, consumption, and potential for meat replacement. The primary outcome is the replacement of dietary meat protein with plant- or insect-based protein from the intervention foods assessed through change in daily meat protein intake, proportion of meat protein to total protein intake, and counts of dinner meals with meat and intervention products.

**Conclusion:**

The results of this study will contribute to research in alternative proteins and explore the effects of long-term exposure of meat replacement.

**Trial registration:**

ClinicalTrials.gov: NCT05156853. Registered 24 December 2021

## Background

Dietary shifts to more sustainable food choices in the daily diet can make an important contribution to reach the target of reducing the environmental impact and greenhouse gas emission in Denmark. Overall, emissions for Nordic diets are estimated yearly at 1.9–2.0 tonnes CO_2_ equivalents with animal products being responsible for about 65–75% of these emissions [1]. Dietary shifts to reduce meat consumption relies on the consumer’s willingness to replace the consumption of meat with that of more sustainable protein sources.

Plant-based diets are viewed by society as a suitable alternative to reduce food-related environmental impact and have gained popularity in the past couple of years. Global retail sales of plant-based meat reached $4.2 billion USD in 2020, up from $3.4 in 2019 [2]. The EU Green Deal’s Farm to Fork strategy promotes the creation of a resilient, safe, and affordable sustainable food system that responds to consumer demands for healthy and environmentally friendly products [3]. Similarly, the Intergovernmental Panel on Climate Change describes sustainable healthy diets as those that “promote… health and well-being; have low environmental pressure and impact; are accessible, affordable, safe and equitable; and are culturally acceptable” and specifically refers to plant-based foods as a part of this diet [4]. The Danish Veterinary and Food Administration recommends eating a plant-rich diet of fruits, vegetables, and legumes while reducing the intake of meat for healthier and more sustainable food consumption [5]. A modified version of the EAT-Lancet diet to better fit Danish dietary guidelines was nutritionally adequate for 6–65 year old individuals, with the exception of vitamin D and iodine [6].

Insects have become another promising alternative protein for human consumption and animal feed with a market estimate of $9.6 billion USD by 2030 [7] and recent legislative evaluations creating a clearer market path for insect-based products. The European Food Safety Authority (EFSA) has evaluated dried yellow mealworms (*Tenebrio molitor*), house crickets (*Acheta domesticus*), and buffalo worms (*Alphitobius diaperinus*) to be safe for human consumption [8–12]. Despite physiological differences between species, edible insects provide the nutritional benefits of animal-based foods [13, 14] with high protein quality [15] and less environmental impact (e.g., less water and land use) than traditional livestock [16], particularly when compared to beef and potentially less than chicken [17]. Additionally, insects can be reared with organic waste materials, such as food waste, distiller’s dried grains, and beer spent grains [18, 19].

Barriers to the consumption of edible insects are complex; low familiarity, food neophobia, and cultural unacceptability drives views of skepticism and disgust [13, 20–25]. Several factors can also influence acceptability and willingness to eat insects, such as age and previous exposure [26–29]. Insect-based food products are mainly marketed as exotic snack products, like whole dried flavored insects, and protein bars which may not be sufficient to encourage integrating insects as a meat replacement. One study showed that very few consumers moved from occasionally tasting insects to regularly eating them [30]. An influx of studies further explore acceptance strategies in varying populations, such as priming [31] and exposure [27, 32–34], as well as improving the sensory profile [35].

Food neophobia is not exclusive to insect-based foods. People often associate meat-inclusive dishes with tradition, values, and a part of complete meal [36]. Possidónio et al. [37] found committed meat eaters showed aversion towards plant-based substitutes, but meat eaters who were concerned with health and nutrition viewed plant-based substitutes (with the exception of lab grown meat) as healthier than red meat.

Interventions with plant-based alternatives have resulted in reduction of meat intake and changes to psychosocial variables, such as increased positive attitudes and reduced meat attachment [38, 39]. Introducing novel proteins for meat replacement presents numerous barriers that can influence how the food is received, such as lack of reliable information, knowledge and cooking skills, and social support [40]. To address this such obstacles, a plant-based menu will act as a control in the study to investigate if the effects of an insect-based dietary intervention differ from other alternative protein sources.

Sustainable Insect Chain (SUSINCHAIN) Work Package 5 aims to develop insect-based foods suited for integration in regular main meals in Europe and to investigate their acceptance, consumption, and potential to replace meat in diets, relative to that of extant plant-based protein sources.

### Objective and hypothesis

The overall objective of this study is to investigate the impact of exposing families (paired participants—an adult and a child) to dinner menus of meals with alternative proteins (insect-based or plant-based products) on dietary pattern, intake of meat, and protein over a 6-week intervention period. The insect-based menu is the experimental exposure, and the plant-based menu is the positive control menu.

The hypothesis is that test menus of meals with alternative proteins will replace the meat consumed during dinner, resulting in maintaining the total protein intake while replacing 20% of the meat protein with alternative protein on a weekly basis. The assumption is that the insect-based menus will replace meat protein similarly or to a larger extent than the positive control group receiving the comparable plant-based menu. The inclusion of the positive control group allows us to isolate the specific impact of exposure to insect-based menu from the exposure to dietary change of more familiar plant-based products. The protein replacement is determined by tailoring the protein content of the experimental products included in the menus of three weekly portions of the alternative protein products to national average levels of meat intake. The assumption is that meat is primarily consumed for lunch and dinner meals.

#### Primary outcome

The primary outcome is the replacement of dietary meat protein with protein from the intervention foods (insect- or plant-based). The co-primary endpoints are changes in the intake of meat protein over the 6-week intervention period and the measures for replacement by the intervention products. The change is assessed as (1) change in intake of total daily amount of meat protein at baseline (prior to receiving the intervention products) and endline (sixth weeks of receiving the intervention products), (2) change in proportion of meat protein of the total protein intake, and (3) counts of dinner meals with meat and alternative protein products during baseline week 0 and during each of the intervention weeks, including the endline assessment during the 6th week of intervention.

#### Secondary outcome

The secondary outcome is change in the sensory evaluation of the intervention foods. The secondary endpoint is changes in the sensory parameters for liking of the intervention food prepared as meals.

The hypothesis is that the liking and acceptance of the novel products will increase over time [27, 41, 42]. Demographic and anthropometric measures, as well as other individual-level characteristics (degree of food neophobia and food disgust, earlier exposure to edible insects), are included as explanatory variables.

## Materials and methods

### Study design

The study is a two-arm randomized equivalence intervention trial. The participants are recruited from families. In each family, one adult and one 8–10 year-old child are enrolled as paired participants. The families are provided products incorporating alternative proteins (insect-based or plant-based) suited to replace meat in dinner meals three times per week, for 6 weeks.

Figure 1 depicts the study flowchart. Recruitment, information meetings, collection of informed consent, and other relevant duties are conducted by the on-site project management team and supervised by the PI. During the recruitment period, interested parents and children will attend an information meeting at the Department of Nutrition, Exercise and Sports of the University of Copenhagen, formally enrolling to participate when signing consent. Subsequently, participants receive instructions for baseline measurements. Baseline measurements are completed during the following week, to estimate habitual protein intake (urine and dietary registrations), food neophobia (questionnaire), food disgust (questionnaire), and previous exposure to edible insects (questionnaire). Participating adults will complete a household characteristics questionnaire and a meat attachment questionnaire. One week later, the participants are returning to the department for random allocation to experimental diets, and distribution of products for the following 2 weeks. During that visit, anthropometric measurements will be collected prior to the start of the dietary intervention. Daily food records (questionnaire) will start during the first week of the dietary intervention up to the final day of the dietary intervention. Intervention week 1 includes the baseline food acceptability and feedback questionnaire, to be completed by the participating adult and child. Intervention week 5 includes the endline food acceptability and feedback questionnaire. During intervention week 6, the paired participants will collect endline urine samples and complete the endline 4-day dietary registrations and end-of-study questionnaires. To aid with retention, reminders are sent to participants to complete the registrations, questionnaire, and prior to appointments.

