### Statistics

In order to measure the 20% replacement of meat in meals with insect- or plant- based alternatives from *x̄* = 14 meals/week to *x̄* = 11.2 meals/week, we will need a sample size of 78 paired participants. This sample size is based on *α* = 0.05, *β* = 0.80, and an assumed *σ* = 7. The standard deviation of the protein intake in the target population is uncertain and the statistical power is therefore based on assumptions. The results of the study will have important scientific value independent of the assumption of statistical power.

Statistical analysis will be used to determine changes in meal patterns as counts of meals with meat and the total protein intake at baseline and endline both within and between the insect and plant groups, hypothesizing no change in total protein intake and 20% replacement of the meat meal using linear models. The same analysis will be conducted both within and between the meat proteins with the insect-based foods at baseline and endline. A Spearman’s rho test will be used to assess perception change (neophobia, exposure, and disgust) before and after the intervention. A paired sample *t*-test (or Wilcoxon test, if not normally distributed) will be used to analyze pre- and post- intervention urine samples.

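### The design is labelled equivalence, but the sample size rests on detecting a fall in meat meals and no margin is stated, so neither between-arm similarity nor maintained protein can be confirmed as planned

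*Protocol article*

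**What the plan says.** All references are to the protocol article.

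- **Study design:** "The study is a two-arm randomized equivalence intervention trial".
- **Objective and hypothesis, between arms:** the assumption is that "insect-based menus will replace meat protein similarly or to a larger extent than the positive control group". This is one-sided: an insect menu that does better would also satisfy it.
- **Objective and hypothesis, total protein:** the menus are expected to replace meat at dinner, "resulting in maintaining the total protein intake while replacing 20% of the meat protein with alternative protein on a weekly basis".
- **Statistics, sample size:** "In order to measure the 20% replacement of meat in meals with insect- or plant- based alternatives", with means of 14 and 11.2 meals per week, "we will need a sample size of 78 paired participants". The basis given is "This sample size is based on *α* = 0.05, *β* = 0.80, and an assumed *σ* = 7".
- **Statistics, analysis:** meat-meal counts and total protein are to be compared over time in each arm and from one arm to the other. The approach is described as "hypothesizing no change in total protein intake and 20% replacement of the meat meal using linear models". Urine samples before and after the intervention are compared by a paired t-test or a Wilcoxon test.

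The article gives no margin for the arm comparison or for total protein, and no rule that sets a confidence interval against one.

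**The concern.** An equivalence trial needs a margin, and its sample size follows from that margin. Here the label says equivalence, the objectives word the arm comparison more like non-inferiority, and the sample size answers a third question: whether meat meals fall by 20%. The first two concern the contrast between menus. The third, as the arithmetic below shows, concerns change within a menu.

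Total protein has a related problem. A t-test, a Wilcoxon test or the usual test in a linear model takes no change as its null hypothesis, so it can reject no change but cannot establish it. The noisier the data, the easier it is to fail to reject.

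At stake is what the trial may conclude about insect against plant menus, and about whether protein intake held up while meat was replaced.

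**Working it through.** **Inputs.** From Statistics: a reduction of 14 − 11.2 = 2.8 meals per week, SD 7, α = 0.05, and the stated β of 0.80 read as power of 0.80. From the abstract and the randomization section: 80 families and two arms, so 78 pairs is taken as a total of 39 per arm. The margins below are assumptions, because the document gives none.

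**1. The plan's own figure (normal approximation).**
- Within-arm change, one-sided: n = (7 × (1.645 + 0.842) / 2.8)² = 38.6, so 39 per arm and **78 in total**. This reproduces the figure.
- Within-arm change, two-sided: 50 per arm, 100 in total. This does not.
- Two-sample difference, one-sided: 2 × 38.64 = 77.3, so 78 *per arm*, 156 in total. The number matches, but not as a total for a trial of 80 families.
- Two-sample difference, two-sided: 99 per arm, 198 in total. This does not.

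Both routes to 78 test for a difference and neither uses a margin. The one that fits the trial's size concerns change within an arm and leaves sidedness unstated.

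**2. Precision of the arm comparison.** SE = 7 × √(2/39) = 1.585. The 90% half-width is 1.645 × 1.585 = 2.6 meals per week, against a targeted effect of 2.8.

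**3. Power for equivalence.** For two one-sided tests at 5% each and a true difference of zero, power = 2Φ(M/SE − 1.645) − 1, or zero where this is negative.
- M = 2.8: 2Φ(0.121) − 1 = 0.097, about 10%.
- M = 1.4: zero.
- Margin giving 80% power: (1.645 + 1.282) × 1.585 = 4.64, which is 4.64/2.8 = 1.66 times the targeted effect.
- Pairs needed for 80% power at M = 2.8: 2 × (7 × 2.926/2.8)² = 107.0, so 108 per arm and 216 in total.

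**4. Power for the one-sided wording.** Non-inferiority at one-sided 5%: Φ(M/SE − 1.645) = 22% at M = 1.4 and 55% at M = 2.8.

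**5. Sensitivity to the SD, 39 per arm.** If 7 is a cross-sectional SD, baseline adjustment with an assumed correlation r gives 7√(1 − r²): 6.06 at r = 0.5 and 5.0 at r = 0.7. An SD of 3.5 is the largest possible for a count of dinners between 0 and 7 per week.

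| SD | SE | 90% half-width | Equivalence power, ±2.8 | Equivalence power, ±1.4 |
|---|---|---|---|---|
| 7 | 1.585 | 2.6 | 10% | 0 |
| 6.1 | 1.373 | 2.3 | 31% | 0 |
| 5.0 | 1.132 | 1.9 | 59% | 0 |
| 3.5 | 0.793 | 1.3 | 94% | 10% |

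**6. What cannot be computed.** No SD is given for meat protein in grams, for meat protein as a share of total protein, or for total protein. Statistics itself calls the protein SD uncertain. The meals-per-week figures do not carry over to these measures.

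**The case against.** The strongest reply is that the article condenses a fuller protocol, that margins and rules of interpretation may be set there or in an analysis plan, and that a linear model already yields the estimate and interval one would want. This stands in part: a missing interpretation rule alone would not be a finding. But the article states its sample-size basis in full, and that basis contains no margin. One supplied elsewhere would not make 78 an equivalence sample size.

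Several stronger readings are tempting and are not supported.

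- *A non-significant result will be read as equivalence or as maintained protein.* The article never says so. It is a risk left open by the wording, not a stated rule.
- *The aims are mutually incompatible.* A within-arm replacement aim and a between-arm comparison can coexist, and the objectives present the latter as an assumption. The real conflict is between the equivalence label and both the one-sided wording and the sizing.
- *The trial's main conclusions all fall.* Total protein is part of the hypothesis but is not a listed primary or secondary endpoint, and the co-primary endpoints are framed as changes.
- *Equivalence power is about 10%.* That holds only for SD 7 and a margin of ±2.8. SD 7 may be too large: if 14 meals means seven lunches plus seven dinners, a count with mean 11.2 has an SD of at most √(11.2 × 2.8) = 5.6. The count among the primary endpoints is of dinners only, which gives the 3.5 used above.

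**Conclusion.** The point holds in this limited form. The stated design and the stated sample-size basis disagree, and the document's methods cannot confirm either similarity between menus or unchanged total protein, because no margin is given. Estimates with confidence intervals remain reportable; what is lost is the confirmatory conclusion.

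The size of the problem depends on two things the document does not settle: the margin and the true SD. At 39 pairs per arm and a true difference of zero, equivalence power at ±2.8 meals per week runs from about 10% (SD 7) to 94% (SD 3.5). At ±1.4 it is no more than about 10% across that range. A margin of 2.8 is generous, since it equals the whole effect the trial seeks. For the protein measures the size is unknown.

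**What to change.** 1. In Study design, remove the word equivalence and describe a randomized trial of within-arm change with between-arm estimation, so that the section agrees with Objective and hypothesis and with Statistics.
2. In Statistics, report the baseline-adjusted insect-minus-plant difference with its confidence interval.
3. Allow a claim of similar or better replacement only if the interval excludes a shortfall as large as a margin that the sponsor chooses and justifies before results are seen. Allow a claim that total protein was maintained only if the interval for the change lies wholly within such a margin. Otherwise report the result as inconclusive.
4. State that the sample size was not derived for equivalence, and that a non-significant result is not evidence of equivalence or of no change.

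If the sponsor prefers to keep the equivalence label, the margin has to be stated and justified and the sample size derived again from it.

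The cost is wording and, if required, an amendment by the route described under Trial status, where recruitment is reported as ongoing. No new data are needed. The downside is that the between-arm and protein-maintenance conclusions may have to be reported as inconclusive.

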**Fig. 1 Fig1:**
[figure not shown]
Flowchart of the study design

### Intervention menu

Three study food products will be delivered per week over the 6-week study period. One of two menus (insect-based or plant-based) will be assigned to the paired participants. A randomly assigned sub-menu (a, b, or c) will determine the order of foods throughout the study. During the first 2 weeks of the study, participants will try each of the six selected food products from their assigned menu. In the following weeks, the assigned sub-menus will provide the same number of meals for each of the food products, with only the assigned order differing between the sub-groups.

#### Portion sizes

The menus are composed of packed portions estimated to on average replace 20% meat protein intake for one adult and one child calculated on a weekly basis using data from 2011–2013 Danskernes Kostvaner [43]. The menus of either insect-based products or plant-based products are provided to the paired participants (one adult and one child) as packed portions dimensioned to provide the amounts of protein set to reach the targeted protein replacement. If family members not enrolled as participants want to be part of the dinner meal, additional portions are provided on request. Based on the assumption that the meat consumption is equally distributed between lunch and dinner meals, the national average amounts of meat protein per meal is set to 13.4 g for adults and 9.7 g for children. The insect-based or plant-based products are provided in portion sizes providing insect protein matching the average meat consumption to provide a full replacement of meat regularly consumed for the three weekly dinner meals.

#### Insect-based foods

Six insect-based products were designed and developed by partners in the SUSINCHAIN project. Production occurred in the appropriate food manufacturing facilities, approved for this type of production. The products include chili-tomato paste (incorporating *Acheta domesticus*) from Bugging Denmark (Copenhagen, Denmark), crispbread (incorporating *A. domesticus*) from Marche Polytechnic University (Ancona, Italy), falafel (incorporating *Alphitobius diaperinus*) from New Generation Nutrition (Den Bosch, Netherlands), minced meat (incorporating *Tenebrio molitor*) from KU Leuven (Leuven, Belgium), spice mix (incorporating *A. domesticus*) from the Technical University of Denmark (Lyngby, Denmark), and sausages (incorporating *A. domesticus* and *A. diaperinus*) from LEITAT (Barcelona, Spain). Criteria was set by the partners so that the developed products were visually and texturally appealing by avoiding whole insects and being familiar and convenient to consumers. Products were subject to sensory testing by project partner Sense Test (Vila Nova de Gaia, Portugal) before being approved for the intervention.

#### Plant-based foods

The plant-based menu will consist of market available products. The plant-based products matched as closely as possible the insect-based products in terms of presentation and nutritional composition. To avoid influence from branding, packaging will be altered.

### Study participants

#### Inclusion criteria

Participants must be healthy, which is determined from the self-reported medical history. All medication that is necessary for the participant’s health or a medical condition and which is not listed in the exclusion criteria may be continued during the study.

Participants must eat meat for dinner at least 5 days a week on average and be willing to consume both insect- and plant-based foods. Participants must be able to talk, read, and understand Danish to properly understand the study procedures.

Adults must have basic computer competency and the household must have freezer capacity for 2 weeks of food.

Children must be between 8 and 10 years old. If a child wants to participate, but their custody holder does not want to participate, another adult from the household can participate with the child. The custody holder is still responsible for the child’s participation in the study.

